## Abstract

**Background:**

Children who witness interparental violence are at a heightened risk for developing psychosocial, behavioral and cognitive problems, as well as posttraumatic stress symptoms. For these children the psycho-educational secondary prevention program 'En nu ik...!' ('It's my turn now!') has been developed. This program includes specific therapeutic factors focused on emotion awareness and expression, increasing feelings of emotional security, teaching specific coping strategies, developing a trauma narrative, improving parent-child interaction and psycho-education. The main study aim is to evaluate the effectiveness of the specific therapeutic factors in the program. A secondary objective is to study mediating and moderating factors.

**Methods/design:**

This study is a prospective multicenter randomized controlled trial across cities in the Netherlands. Participants (N = 140) are referred to the secondary preventive intervention program by police, social work, women shelters and youth (mental health) care. Children, aged 6-12 years, and their parents, who experienced interparental violence are randomly assigned to either the intervention program or the control program. The control program is comparable on nonspecific factors by offering positive attention, positive expectations, recreation, distraction, warmth and empathy of the therapist, and social support among group participants, in ways that are similar to the intervention program. Primary outcome measures are posttraumatic stress symptoms and emotional and behavioral problems of the child. Mediators tested are the ability to differentiate and express emotions, emotional security, coping strategies, feelings of guilt and parent-child interaction. Mental health of the parent, parenting stress, disturbances in parent-child attachment, duration and severity of the domestic violence and demographics are examined for their moderating effect. Data are collected one week before the program starts (T1), and one week (T2) and six months (T3) after finishing the program. Both intention-to-treat and completer analyses will be done.

**Discussion:**

Adverse outcomes after witnessing interparental violence are highly diverse and may be explained by multiple risk factors. An important question for prevention programs is therefore to what extent a specific focus on potential psychotrauma is useful. This trial may point to several directions for optimizing public health response to children's exposure to interparental violence.

**Trial registration:**

Netherlands Trial Register (NTR): NTR3064

## Background

Interparental violence is a considerable worldwide problem; for example in the United States alone 16% of all children (2-17 years of age) witness partner assault some time in their childhood [1]. The latest estimates within the Netherlands are that 12% of all adolescents have witnessed interparental violence in their lives [2]. The consequences of witnessing interparental violence are severe; meta-analyses show that children exposed to interparental violence experience emotional, behavioral and cognitive problems [3,4]. Children exposed to interparental violence may show short-term maladjustment as well as develop long-term mental health problems. For example, adults who witnessed interparental violence as children are two to four times more likely to report problems with alcoholism, drug use and depression [5]. Despite potential severe and lifelong consequences of witnessing interparental violence, few carefully designed interventions for children exposed to interparental violence have been developed, and even fewer of these programs have been thoroughly tested [6]. Questions remain therefore about the kind of interventions that may prevent or limit adverse consequences for children exposed to interparental violence.

According to Cummings and Davies' (2010) emotional security hypothesis, exposure to destructive interparental conflict increases children's vulnerability to psychological problems by undermining their confidence in the interparental relationship and the security they find in the family. Direct effects derive from experiencing the conflicts themselves; indirect effects derive from experiencing deteriorated parenting and parent-child interaction due to the effects of conflict on the parents. Preserving feelings of emotional security is a salient psychological goal for children, governed by emotional and behavioral regulation and cognitive representations. These response processes may to some degree help to defend their physical and psychological safety, but may have long-term costs or break down in the end. Children's emotional and behavioral regulation in the face of interparental violence was longitudinally associated with children's externalizing and internalizing problems [7].

Children may embark on a developmental pathway towards psychopathology, even after interparental conflict has stopped. These effects are likely to depend on specific family, parent or child factors. The degree of children's adjustment problems may depend on the duration and severity of the domestic violence [3,8], parenting and psychological functioning of the parent [9]. Research is inconsistent regarding the impact of demographic variables, such as age, gender and ethnicity on children's adjustment after witnessing interparental violence [10,11].

Based on the emotional security perspective, there is a need for preventive interventions that restore security in the family system(s) that children find themselves in, and that support the parents and improve parent-child interaction [7]. Such programs may diminish the long-term consequences of interparental violence.

Trauma theory [12] focuses on how experiences that elicit overwhelming fear alter affective functioning. Usually, distress after a frightening experience is transient. If distress persists, a posttraumatic stress disorder (PTSD) may develop. Symptoms of a posttraumatic stress disorder in adults as well as in children include 1) re-experiencing the trauma, as flashbacks or nightmares; 2) persistent avoidance of stimuli associated with the trauma and emotional numbing; and 3) persistent hyperarousal, evidenced by sleeping and concentration problems, irritability and hypervigilance [13]. Therapeutic intervention therefore focuses on readjusting affective responses to trauma-related thoughts and memories, as well as reminders. Techniques are therefore not only based on trauma theory, but also on social cognitive theory [14], for example within Trauma Focused Cognitive Behavioral Therapy (TF-CBT) for children diagnosed with PTSD. Components used in TF-CBT for children are psycho-education, relaxation skills, affective modulation skills (e.g. identification of feelings), cognitive coping and processing, enhancing future safety and development, and trauma narrative. Affective functioning in children is closely aligned with relationships with parents, and therefore TF-CBT includes psycho-education of parents, parenting skills training and conjoint child-parent-sessions, in which the child shares the trauma narrative and other family issues are addressed [15]. The effectiveness of TF-CBT is well established for victims of sexual abuse [16]. For children exposed to interparental violence, Cohen and her colleagues [17] compared in a randomized controlled trial a brief (8 weeks) individual Trauma-Focused Cognitive Behavioral Therapy to Child Centered Therapy (CCT) and found that children who completed TF-CBT showed improvement in PTSD symptoms and anxiety symptoms relative to children who completed CCT.

Further support for the role that parent-child relationships may have for risk, resilience and recovery in the case of exposure to interparental conflict comes from attachment theory [18]. Therapy with child and parent includes components such as assisting the parent with accurate interpretation of the child's feelings and actions, providing emotional support to parent and child, and developing a joint parent-child narrative about the trauma. The effectiveness of attachment theory in intervention for preschoolers exposed to interparental violence, has been studied by Lieberman and her colleagues in a randomized controlled trial. They found that a 50-week child parent psychotherapy program reduced traumatic stress symptoms and improved behavior compared to case management with individual psychotherapy.

One problem with therapy for children exposed to interparental violence is that access to such therapy is contingent on linking behavioral dysfunction with exposure to the violence. A child has to be seen as functioning problematically and the professional has to be aware of the role of the violence in behavioral dysfunction before a child will be referred to such therapy. Also, children and their families differ in their tendency to seek treatment after exposure to traumatic events [19]. Therefore, a secondary prevention program, 'Kids' Club', was developed in the United States [20] that is offered to families with children who seek help or refuge after interparental violence, or who have been involved with social services or police because of family violence. Children do not have to exhibit problematic functioning for participation. The program was mainly based on insights from trauma theory, later including parallel parent sessions, given recognition of the importance of parents for resilience and recovery. Effectiveness of 'Kids' Club' has been studied in a quasi-experimental study by Graham-Bermann and her colleagues [21]. They found that this community based group intervention of 10 sessions was effective in reducing externalizing and internalizing behavior problems, compared to a waitlist group. Furthermore, children in the condition with parallel parent and child sessions, showed greater reduction in behavioral problems compared to children following a similar intervention but with only child sessions and no parent sessions [21]. These results support the inclusion of parents in interventions for children exposed to interparental violence. The original child sessions of 'Kids' Club' have been used as a basis for the development of a secondary prevention program in the Netherlands. Independent from 'Kids' Club', the Dutch program was further developed by including nine parallel parent sessions. This program is called 'En nu ik...!' ('It's my turn now!'). Lamers-Winkelman showed in a study with a quasi-experimental design that children, after participation in the program 'En nu ik...!', exhibited less internalizing and externalizing behavioral problems and less posttraumatic stress symptoms [22].

To our knowledge, no randomized controlled trial on the effectiveness of this secondary prevention program has been carried out. The only two randomized controlled trials studying therapeutic interventions for children exposed to interparental violence [17,18], suggest that a focus on trauma as well as on the parent-child relationship in therapy is important to reduce adjustment problems in children. The question is whether this may be true for secondary prevention programs as well, because the population for preventive intervention is likely to be more diverse in symptomatology at referral than the population for therapeutic intervention. Another question regards the effect of specific factors aimed at the traumatic experience compared to nonspecific factors. Previous trials compared different specific factors or different combinations of specific and nonspecific factors. As a result, it is unknown whether for children often exposed to multiple risk factors besides interparental violence [7], a focus on the traumatic experience can be shown to have added value.

To study the effectiveness of the secondary prevention program 'En nu ik...!' and to assess the need for a specific focus on trauma in interventions, a randomized controlled design is used within this study. Parents and children are randomly assigned to either the existing secondary prevention program or an alternative control program. This alternative program has been developed for this study and has the same structure as the secondary prevention program, but has been stripped of any specific factors, does not include a trauma-focus and is solely based on nonspecific factors in interventions, such as positive attention, recreation, distraction, warmth and empathy of the therapist, and social support among group participants [23].

In all aforementioned studies about the effectiveness of interventions for children exposed to interparental violence, only questionnaires were used to gather information, and in the study of Lamers-Winkelman (2003) [22] and Cohen et al. (2011) [17] no follow-up was conducted. In this study, observational measures as well as questionnaires for parent, child and teacher, are used to prevent a reporting-bias, and follow-up assessments are included to assess long-term consequences of participation.

In addition to the study of program effectiveness, evidence for mechanisms of change and predictors of effectiveness may further support the intervention design. Graham-Bermann and her colleagues (2011) pioneered the study of specific mediators and moderators, focusing on parenting and mental health of the mother as mediators and degree of exposure to family violence and demographic variables as moderators [10]. The current study will focus on parent-child interaction, emotional security and taught skills (coping strategies, feelings of guilt, the ability to differentiate and express emotions) as mediators and mental health of the parent, parenting stress, disturbances in parent-child attachment, duration and severity of the domestic violence and demographics as moderating variables.

### Trial objective

In order to justify broad implementation of a protocol led psycho-educational secondary preventive intervention program for children exposed to interparental violence in the Netherlands, empirical evidence is needed to show that children benefit from participation in this program. The present study will add to this evidence with a randomized controlled trial (RCT). Effectiveness is measured in terms of less posttraumatic stress symptoms, less internalizing and less externalizing behavioral problems. Because of the design of this study in which children in a trauma-focused intervention program are compared to children in a control program with only nonspecific factors, this study will provide insight in the need for trauma-focus in intervention. This knowledge can be used to improve care for children exposed to interparental violence. Potential mediating and moderating variables are investigated in order to evaluate underlying mechanisms of change and to identify predictors of effectiveness.

## Methods

### Study design

The study is designed as a multicenter trial with concealed random allocation to the experimental arm which will receive the secondary prevention program 'En nu ik...!' ('It's my turn now!') and the control arm which will receive a program similar in form, but containing only nonspecific elements, called 'Jij hoort erbij' ('You belong'). The multicenter design was chosen to improve generalizability of the study results. Eight organizations in seven cities in urban and rural regions of the Netherlands have agreed to participate in this research.

### Randomization

An independent researcher will make the allocation schedule with a computerized random number generator. The random allocation list will be generated in blocks of no less than two, depending on the number of participating groups per time period. The numbers on the list will be paired with the groups in order of the date on which the groups start. The condition of the group will be disclosed to the participating organizations and to the researchers two weeks before the start of the program. Potential contamination of the intervention and control group will be avoided by restricting recruitment to one child per family.

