Each group is randomly assigned to either the intervention or the control arm. Parents and children are given the details about the program into which they are randomized. Parents and children who participate in the study are invited to the setting (e.g. community centre, mental health clinic) at which the program (intervention or control) takes place one week before the program starts. They are asked to fill out questionnaires (T1). A week later the program starts for all parents and children. One week (T2) and six months (T3) after the end of the program parents and children who take part in the study are again invited to fill out questionnaires and participate in two observation tasks. If parents or children have trouble filling out the questionnaires, a trained masters student or an interpreter will assist. To check up on parents in the period between T2 and T3, parents are contacted by phone two times. Figure 1 shows the different stages of the research procedure and gives an overview of the instruments used at each assessment.

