**Figure 1 F1:**
[figure not shown]
**Research procedure**. After informed consent is obtained, 2/3 of all parent-child dyads will be randomized into the experimental arm and 1/3 into the control arm. Parents and children are asked to fill out questionnaires (parent: TSCYC, CBCL, Questionnaire about duration and severity of domestic violence, demographic questionnaire, IES-R, HADS, PSI; child: CDI, TSCC, Questionnaire for children how to cope with difficult situations) at the first assessment (T1). A week later the program starts for all parents and children. One week (T2) and six months (T3) after the end of the program parents and children who take part in the study are again invited to fill out questionnaires and participate in two observation tasks (FIT and AEED). To check up on parents in the period between T2 and T3, parents are contacted by phone two times. At all assessments the teacher is also sent a questionnaire.

Parents receive €15,- after completing the first assessment, €25,- after participating in the program and completing the second assessment and €40,- after completing the follow up assessment. Children receive a gift after each assessment.

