### Blinding

Parents, children, social workers as well as the researchers are blind to group allocation until two weeks before the start of the program. The condition is not disclosed earlier to avoid a bias in the intake procedure because of prior knowledge about the condition. Parents and children agree to participate in the study before randomization and without knowing in which arm they will be enrolled. Both programs are presented as useful programs by discussing the specific and/or nonspecific factors that can be of benefit to children and parents exposed to interparental violence. Every ID-number assigned to a parent-child-dyad is independent of the condition. The researchers coding the observation tasks and analyzing the data will be blind to the group condition of parents and children, as well as assessment (T1, T2, T3).

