### Sample size calculation

The total sample size is based on the expected differences in outcome measures between children participating in the secondary prevention program 'En nu ik...!' and the control program 'Jij hoort erbij'. Because the effect of the intervention program has been tested before in a non-experimental design [22], a conservative estimate of f = 0,25 [59] is made about the effect size. Based on an alpha of .05, a power of .80 in a two tailed test, 48 subjects in each condition are needed.

To answer the research questions concerning the influence of potential mediators and moderators on the effectiveness of the secondary prevention program, several multiple regression analyses with different predictors will be performed. Based on an alpha of .05, an expected medium effect size of f^2 ^= 0.15 and a N = 90 we will be able to achieve a power of .80 for a model with up to five predictors. In smaller models of up to two predictors it will also be possible to draw conclusions about the independent contribution of each predictor.

Because of the tumultuous time these families are in we expect a relatively high drop-out rate of around 45% from T1 to T3. For this reason, we aim to recruit 250 children and parents.

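### Allocation blocks as small as two groups cannot hold the 2:1 ratio in Figure 1 and, if balanced with staggered starts, can give away the second group's arm early

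*Protocol article*

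**What the plan says.** The unit of allocation is the therapy group. Procedure: "Each group is randomly assigned to either the intervention or the control arm".

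Randomization describes how the list is built and used. An independent researcher generates it by computer. On block size: "The random allocation list will be generated in blocks of no less than two, depending on the number of participating groups per time period". On its use: "The numbers on the list will be paired with the groups in order of the date on which the groups start". On release: "The condition of the group will be disclosed to the participating organizations and to the researchers two weeks before the start of the program".

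The Figure 1 legend gives the ratio: "2/3 of all parent-child dyads will be randomized into the experimental arm and 1/3 into the control arm". Sample size calculation gives the arm sizes: "Based on an alpha of .05, a power of .80 in a two tailed test, 48 subjects in each condition are needed".

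Blinding explains the late release: "The condition is not disclosed earlier to avoid a bias in the intake procedure because of prior knowledge about the condition". It adds that "Parents and children agree to participate in the study before randomization and without knowing in which arm they will be enrolled". Study design calls the allocation concealed.

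The article does not give the ratio within a block, say who knows the block sizes, say whether blocks run within or across organizations, or say when a group's intake closes. A condensed article may leave these to the full protocol, and their absence is not the point here.

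**The concern.** Two things in the stated text do not fit together.

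First, the block rule lets block size follow however many groups run in a period, down to two. Most of the sizes this can produce cannot carry a 2:1 split of groups, and the article does not say how the Figure 1 ratio is then reached. The sample size section is written for equal arms.

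Second, the rule combines a very small minimum block, a size tied to something organizations and researchers may be able to observe, list positions filled by start date, and release of each arm before that group starts. Together these can make a later group's arm deducible before its own release date.

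What is at stake is selection at intake. Organizations run the intake and ask for consent (Procedure). The exclusion criterion is a judgment about whether behavior would disturb the group (Inclusion and exclusion criteria). Families who decline the study may still join the program (Procedure), so steering of study consent would be hard to see afterwards. Consent before randomization does not protect against this if staff can already work out the arm.

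**Working it through.** **Inputs.** Minimum block of two groups, sized by groups per period; list used in order of start date; arm released two weeks before start (all Randomization). Ratio 2/3 to 1/3 (Figure 1 legend). Groups randomized (Procedure). 48 per condition, f = 0.25, alpha .05 two-tailed, power .80 (Sample size calculation).

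**Step 1: the plan's own figure.** For the between-groups effect in a repeated-measures ANOVA with equal arms, the noncentrality is λ = f²·N·m / (1 + (m − 1)ρ), with m measurements and correlation ρ. With m = 3 and ρ = 0.6 this needs 48 per arm; with m = 2 and ρ = 0.5 it needs 49, and power at 48 is 0.799. The ρ values are assumptions, as the article gives none. So 48 can be reproduced, and it is an equal-arm figure: 48 + 48 = 96, ratio 1:1.

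**Step 2: which blocks can hold 2:1.** A block of b groups needs 2b/3 intervention groups, which must be a whole number.

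| Block size b | 2b/3 | Exact 2:1 possible? |
|---|---|---|
| 2 | 1.33 | no |
| 3 | 2 | yes |
| 4 | 2.67 | no |
| 5 | 3.33 | no |
| 6 | 4 | yes |
| 7 | 4.67 | no |
| 8 | 5.33 | no |
| 9 | 6 | yes |

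The ratio in Figure 1 is stated for dyads, not groups. A 1:1 split of groups would give 2:1 in dyads only if intervention groups held on average twice as many families. Both programs have the same maximum of eight, and nothing in the article suggests such a difference.

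**Step 3: can blocks of two reach 2:1 on average?** Only if they are not all balanced. For example, use 1:1 with probability 2/3 and 2:0 with probability 1/3. Expected intervention groups per block = (2/3)·1 + (1/3)·2 = 4/3, and 4/3 of 2 is 2/3. In that mix:

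- First group is intervention with probability (2/3)(1/2) + 1/3 = 2/3. The second is then intervention with probability (1/3)/(2/3) = 0.5, so it is not predictable.
- First group is control with probability 1/3. The second is then intervention for certain.

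**Step 4: timing.** Let the two groups of a balanced block of two start at s1 and s2. The first arm is released at s1 − 2 weeks and fixes the second, whose own release is at s2 − 2 weeks. The second arm is deducible early by (s2 − 2) − (s1 − 2) = s2 − s1. With the same start date the gap is zero.

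**Step 5: share of groups with a deducible arm.** For a block of a intervention and b control groups, with known block size and staggered starts, the expected share is [a/(b + 1) + b/(a + 1)] / (a + b).

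- 1:1, block of 2: (1/2 + 1/2)/2 = 50%.
- 2:1, block of 3: (2/2 + 1/3)/3 = 44%.
- 2:2, block of 4: (2/3 + 2/3)/4 = 33%.
- 4:2, block of 6: (4/3 + 2/5)/6 = 29%.
- 3:3, block of 6: (3/4 + 3/4)/6 = 25%.

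Blocks of three fit the ratio but, used alone and known, are nearly as predictable as blocks of two. Matching the ratio is therefore not enough; sizes must also vary and be hidden.

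**The case against.** The strongest reply is that two is a floor, not a fixed size. Blocks of 3, 6 or 9 are permitted and can hold 2:1. A reader might infer that the procedure and Figure 1 can never both be followed; the text does not support that. What stands is narrower: the rule also permits blocks that cannot hold the ratio, and it lets the number of groups in a period decide which are used.

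The two halves of the point also cannot both be pressed to the full on the same block. Certain prediction of the second group needs a balanced 1:1 block. If blocks of two are unbalanced so as to average 2:1, prediction is only partial (step 3). This is correct, and the two halves should be read as alternatives. Under one, the ratio is not that of Figure 1; under the other, the arm is still sometimes given away.

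A reader might also infer that intake was in fact compromised. The article does not show it. Early deduction needs staff to know or infer the block size, groups in a block to start on different dates, and the later group's intake to be still open. Eight organizations in seven cities take part; if blocks run across them, the next list position may belong to a group elsewhere. Late release and an independent list-maker are genuine safeguards.

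The figure of 48 per condition may be read as a minimum for the smaller arm. At 2:1 that would mean 48 + 96 = 144, close to the 140 children named under Study population. So that section is not a flat contradiction by itself, but it does not state 2:1 either.

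Finally, it is tempting to claim a loss of power from the unclear ratio. That is not supported. The planned analysis is a repeated-measures ANOVA whose correlation is not given, and a plain t-test contrast would not represent it. No power claim is made here.

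**Conclusion.** The point holds in a limited form. It is certain that a block of two groups, or of any size not a multiple of three, cannot be 2:1. The block rule as written therefore does not assure the Figure 1 split, and three sections need to be brought into line on one ratio.

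The concealment weakness is a conditional risk, not a demonstrated breach. At its largest, half of all groups have a deducible arm. That figure assumes balanced blocks of two throughout, known or inferred block size and staggered starts. It falls as blocks grow, and to nothing for groups of one block that start together. Where the conditions are met, the protection of intake claimed under Blinding is weakened for as long as the gap between starts.

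**What to change.** - State one allocation ratio, for groups, and use it in Randomization, the Figure 1 legend and Sample size calculation.
- Generate the remaining list in randomly varied block sizes that fit the ratio: for example 3 and 6 groups if 2:1 is meant, or 4 and 6 if 1:1 is meant. Other compatible mixes would also serve.
- Use no blocks of two, and do not tie block size to the number of groups in a period.
- Keep block sizes from the organizations and the researchers.

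The cost is small. The independent researcher regenerates the list for groups not yet allocated; data collection is already in progress (Status of the trial), so earlier groups are unaffected. Ethical considerations foresees amendments for changes in procedure. Balance within a time period becomes slightly less exact: a period with only two groups may see both in the same arm. Closing the intake of every later group in a block before an earlier arm is released is not asked for, because it could delay families.
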